#### Metabolic and inflammatory biomarkers

Serum samples are taken, centrifuged and stored at −70°C at Linköping University’s Biobank Facility. They will be analysed for insulin-like growth factor I, and its binding proteins I and II (immunoenzymometric assay kit, Medix Biochemica, Finland, and ELISA kit, My Biosource, San Diego, USA, respectively), copeptin, midregional pro-atrial natriuretic peptide (MR-proADM) and midregional pro-adrenomedullin (MR-proANP) (time-resolved amplified cryptate emission technology assay, Brahms Kryptor, Henningsdorf, Germany) and leptin (Milliplex MAP Gut hormone panel, Merck Millipore, MA, USA).^50^,^54^ These biomarkers are selected as they have been linked to the development of infant macrosomia, pre-eclampsia and infant growth restriction, as well as the postpartum development of type 2 diabetes or cardiovascular morbidity and mortality^5153^,^56^; however, other biomarkers may also be considered due to new knowledge at the time of the analyses.

#### Maternal Cardiometabolic risk profile one year postpartum

A fasting blood sample is taken and plasma glucose, HDL-cholesterol, and triglycerides, serum insulin and insulin resistance (HOMA-IR) are assessed at the Department of Clinical Chemistry, Linköping University Hospital, as previously described.^22^ Waist circumference is measured at the umbilical location with a tape measure at the end of a normal expiration. The systolic and diastolic blood pressure are measured in a sitting position using an electric sphygmomanometer (ProBP 3400 series, WelchAllyn, NY, USA) with standardised procedures. Thereafter, based on these variables, a cardiometabolic risk score for each woman will be calculated using commonly applied standards.^57 58^ Also, to evaluate the microvascular function in women with previous GDM, a forearm skin comprehensive microcirculatory assessment will be performed using the PeriFlux PF6000 EPOS (Enhanced Perfusion and Oxygen Saturation) system measuring oxygen saturation and total speed perfusion. The collection of data in absolute units facilitates comparison of data between individuals, not possible with traditional laser Doppler techniques.^59^ Impaired microvascular dysfunction was recently identified in women with previous pre-eclampsia,^60^ and it has also been shown to be associated with increased cardiovascular risk profiles such as a higher SCORE2.^61^

#### Economic evaluation

A within-trial cost-effectiveness analysis^61^ in 2025 Swedish Krona will be conducted from a public healthcare system perspective, comparing the intervention to a standard care comparator. Costs will include intervention costs, other healthcare costs (eg, telephone calls, hospital visits) and will be estimated using unit costing principles and trial records, administrative data and published sources. Health-related quality of life will be measured using commonly applied questionnaires (AQoL-4D) (http://aqol.com.au/index.php/aqolinstruments) and incremental cost-effectiveness ratios will be estimated (including cost per quality-adjusted life year (QALY) gained, cost per percentage increase in glycaemic control, cost per unit improvement in Swedish Healthy Eating Index score, costs per unit improvement in maternal cardiometabolic risk factors). Non-parametric bootstrapping using 1000 samples will characterise uncertainty, and results will be presented on cost-effectiveness planes. Sensitivity analyses will moreover explore the robustness of results when varying key input parameters. For estimation of long-term consequences, beyond the trial period, decision analytical modelling will extrapolate, for example, cardiometabolic risk outcomes using Markov modelling, and employing trial data with evidence from external sources.^61 62^

#### Process and Scalability evaluation

At the end of the intervention (gestational weeks 37–38 and 1 year postpartum), women in the intervention group complete a questionnaire on their overall satisfaction with the app, namely their use and perceptions in terms of usability, design, and features in accordance with our previous studies.^22 44^ Correspondingly, semistructured interviews (audio) are conducted within a subsample of women in the intervention group (n=15–20 end of pregnancy as well as 1 year postpartum) and healthcare professionals (n=10–20) with different roles in the GDM treatment process (midwife, endocrinologist, dietician) to gain additional insight into their perceptions of the SPARK app and clinician portal and its potential for implementation at scale, including barriers and facilitators for such an implementation. All interviews will be transcribed and analysed using thematic analysis.^63^

### Statistical analyses

All analyses will include participants in the groups to which they were randomised (intention-to-treat). We will conduct both available data analyses and analyses with data imputed using multiple imputations with chained equations^64^ (using 200 imputed datasets generated using 30 iterations). We will use multilevel regression with adaptive intercepts for clinics and estimate models using Bayesian inference.^65^ All intercepts and covariates will be given Student’s t priors, and dispersion parameters will be given half-Student’s t priors. The priors will be centred at 0 with a scale of 2.5 and 3 degrees of freedom. For reporting purposes, we will use medians of posterior distributions as point estimates of effects together with 95% compatibility intervals represented by the 2.5 and 97.5 percentiles of the posterior distributions.

For each outcome, we will calculate the posterior probability of two cases:

The posterior probability that the estimated effect favours the intervention group.The lower and upper bound of effect estimates symmetrically around the null which most closely includes 95% of the posterior distribution.

The first case is a straightforward contrast of outcomes between groups and concerns the posterior probability of one group having better outcomes than the other (note that the posterior probability that the estimated effect favours the control group is one minus the posterior probability of the estimated effect favouring the intervention group). The second case concerns the posterior probability of the two groups having similar outcomes. We will identify which range of effects, symmetrically around the null, include 95% of the posterior distribution. For instance, for the main outcome TIR, we will identify the OR range (eg, 1/1.2 and 1.2 ORs) which most closely includes 95% of the posterior distribution.

This contrast has implications for implementation decisions as the two treatments contrasted (SPARK; standard care) have different costs and resource requirements associated with them.

#### Models

For the primary outcome TIR, we will use beta regression and report on the estimated OR with respect to group allocation. We will use linear regression for all other outcomes apart from the introduction of metformin/insulin treatment, adverse obstetric and neonatal outcomes, and adherence to the measurement protocol for daily glucose. The introduction of metformin/insulin treatment will be modelled using ordinal regression (no treatment<metformin<insulin), adverse outcomes will be modelled using negative binomial regression (counting the number of incidences adverse outcomes), and average measurement protocol adherence will be estimated using beta regression. Models will be adjusted for gestational week at baseline, age, pre-pregnancy Body Mass Index (BMI) (underweight and normal weight vs overweight and obese), previous GDM diagnosis, baseline HbA1c, as well as baseline measures of each respective outcome where available. For models of gestational weight gain, we will, in accordance with our previous trials,^22^ fit follow-up weight in gestational weeks 37–38 on group allocation and adjust for baseline weight as it is more robust against regression toward the mean. When relevant we will also additionally adjust for educational attainment (university degree vs no university degree).

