### Randomisation and blinding

After baseline measurements have been completed, participants are randomised in a 1:1 ratio to either the intervention (SPARK mHealth intervention) or the control group (standard care). Randomisation will be based on restricted randomisation, generated through STATA and administered by study personnel through sealed envelopes to preserve allocation concealment. Due to the design of the study with a digital intervention, participants and healthcare personnel are not blinded to their group allocation.

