### Sample size

We conducted a Monte Carlo study to estimate the number of participants we need to recruit. We simulated scenarios where the difference in TIR between groups at follow-up was five percentage points, which is of clinical relevance in diabetic women to lower the risk of adverse pregnancy outcomes.^66^ The differences between groups that we simulated started from 70% TIR in the control group and 75% in the intervention group to 90% TIR in the control group and 95% in the intervention group. We used an SD of 12 percentage points in both groups in all simulations. Aiming for a power of 0.8 at the 0.05 significance level, we found that with 360 women completing follow-up we will have enough power to detect a statistically significant effect in all the scenarios simulated. Based on our previous interventions,^22^ we expect a dropout rate of 10%–15% and will therefore recruit 412 participants. It should be noted that our analyses follow a Bayesian paradigm where null-hypothesis testing is not the basis for scientific inference; thus, a predetermined sample size to protect against type I and II errors is not required. Therefore, the function of our power calculation is only to give a target for recruitment.

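### The sizing holds the SD of TIR at 12 points in both arms, but beta regression in its default single-precision form ties the SD to the mean; at about 80–90% TIR this overstates the primary OR and its 95% interval under-covers

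*Protocol article*

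**What the plan says.** Under Models, the article analyses TIR as follows: "For the primary outcome TIR, we will use beta regression and report on the estimated OR with respect to group allocation". Average adherence to glucose sampling is also to be analysed by beta regression. Under Statistical analyses, one general sentence covers all models: intercepts and covariates receive Student's t priors, and "dispersion parameters will be given half-Student’s t priors". No covariate or group term is attached to the dispersion of the beta models, and the article does not say how TIR values at or near 100% enter the likelihood.

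Under Sample size, "We simulated scenarios where the difference in TIR between groups at follow-up was five percentage points". The scenarios "started from 70% TIR in the control group and 75% in the intervention group to 90% TIR in the control group and 95"%. The spread was held constant: "We used an SD of 12 percentage points in both groups in all simulations". The same section says that the calculation serves only to set a recruitment target.

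**The concern.** In a beta model with one precision parameter, the SD is a function of the mean. If two arms have different means and the same SD, the common-precision model is wrong for those data. The likelihood then uses the mean parameter to absorb part of the mismatch in spread. This is a bias, so a larger trial does not remove it.

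The quantities at stake are the ones the article names as its inference for the primary outcome: the OR, its 95% compatibility interval, the posterior probability that SPARK is better, and the symmetric range around the null used to judge similarity. The article ties these contrasts to implementation decisions. A related risk arises if the arms differ in spread but not in mean, because the model can then report a difference in mean TIR that does not exist.

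**Working it through.** **Inputs.** From Sample size: difference 5 points, SD 12 points in both arms, range 70/75% to 90/95%, target power 0.8 at the 0.05 level (taken as two-sided), 360 completers. From Randomisation and blinding: 1:1 allocation, so 180 per arm. The steps 75/80%, 80/85% and 85/90% are assumed; the article names only the two ends.

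**The plan's own figure.** A plain comparison of two means needs 2 × (1.960 + 0.842)² × 12² / 5² = 90.4, or 91 per arm (182 in total). The stated 360 is not reproduced as the number for 80% power; at 180 per arm power is 97.7%. The 412 recruited agrees with 360 / (1 − 0.125) = 411.4, rounded up. Power is therefore not the issue here.

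**Precision implied by a constant SD.** For a beta variable, precision = mean × (1 − mean) / SD² − 1, with SD² = 0.0144.

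- 70%: 0.2100 / 0.0144 − 1 = 13.6
- 75%: 0.1875 / 0.0144 − 1 = 12.0
- 80%: 0.1600 / 0.0144 − 1 = 10.1
- 85%: 0.1275 / 0.0144 − 1 = 7.9
- 90%: 0.0900 / 0.0144 − 1 = 5.3
- 95%: 0.0475 / 0.0144 − 1 = 2.3

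The two arms are close at 70/75% (13.6 and 12.0) and far apart at 85/90% (7.9 and 5.3).

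**True ORs.** Odds are mean / (1 − mean). For example, at 80/85% the OR is 5.667 / 4 = 1.417, and at 85/90% it is 9 / 5.667 = 1.588.

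**Simulation.** Beta-distributed TIR, 180 per arm, 1000 runs per scenario, the article's priors, normal approximation to the posterior, no covariates or clinic intercepts. Two treatments of values near 100% were used: clipping at 10⁻⁶ from the boundary, or rounding to 1/1344 (14 days × 96 readings) and then shrinking by (359y + 0.5) / 360. Cells show median OR and 95% interval coverage.

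| Scenario | True OR | Common precision, clipped | Common precision, shrunk | By arm, clipped | By arm, shrunk |
|---|---|---|---|---|---|
| 70/75 | 1.286 | 1.295, 96.0% | 1.293, 94.2% | 1.281, 95.8% | 1.278, 94.5% |
| 75/80 | 1.333 | 1.363, 94.2% | 1.362, 94.0% | 1.328, 95.7% | 1.329, 95.4% |
| 80/85 | 1.417 | 1.499, 90.0% | 1.481, 91.7% | 1.415, 95.1% | 1.400, 94.1% |
| 85/90 | 1.588 | 1.887, 56.0% | 1.759, 82.5% | 1.578, 96.2% | 1.570, 92.7% |
| 90/95 | 2.111 | 3.067, 3.9% | 2.046, 98.2% | 2.026, 92.4% | 1.897, 80.9% |

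Maximum-likelihood runs with clipping at 1/2688 agree. Common precision gave 1.50 with 88.5% coverage at 80/85% and 1.84 with 66% at 85/90%; precision by arm gave 1.42 with 95% and 1.59 with 93%. A further set of runs put common-precision coverage at 80/85% at 86–88%.

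The large-sample limits of the common-precision OR are 1.506 at 80/85% and 1.896 at 85/90%, which confirms that the bias does not shrink with more data. The direction at these two steps does not depend on TIR being beta distributed. Logit-normal data with the same mean and SD give limits of 1.454 and 1.673, and censored-normal data with shrinkage give 1.575 and 1.686.

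**Equal means, unequal spread.** With SD 12 in one arm and 10 in the other (an assumption; the article gives no such figure), the common-precision interval excludes OR = 1 in about 13–17% of trials at mean 80%, 25–27% at 85% and 42–47% at 90%. With precision by arm the figure is about 4–6%. The narrower arm is made to look worse, with a median OR of about 0.90 at 85%. With equal means and equal SDs, the common-precision model rejected in 5.6%, 4.2% and 0.6% of 500 runs at 70%, 90% and 95%.

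**The case against.** The strongest reply is that the article never says the TIR model has a single precision. It is a condensed account, its dispersion sentence is plural and covers every model, and an analysis plan not shown may already let precision differ by arm. This stands as a limit: common precision is the default meaning of the stated model, not a stated choice.

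Second, SD 12 in both arms is a sizing convenience, not a forecast, and the article says that sizing sets only a recruitment target. A common precision would need the SD to fall only modestly as TIR rises: from 12 to √(0.1275 / 11.11) = 10.7 points between 80% and 85%, or to √(0.0900 / 8.854) = 10.1 between 85% and 90%. That is plausible for a bounded percentage. So the distortion is conditional on the article's own spread assumption and is not a prediction for the trial. It remains the only spread assumption the article offers, and a model that allows either pattern costs little.

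Third, neither end of the stated range supports a general claim. At 70/75% the effect is negligible, and at 90/95% precision by arm with clipping at 1/2688 covers worse than common precision (84% against 95%). This is correct. It means the boundary has to be dealt with as well.

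Fourth, the simulations omit the planned covariates and clinic intercepts and so treat the marginal SD as the conditional one. The size of the bias in the full model could differ.

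**Conclusion.** The point holds in a limited form. If TIR has an SD of 12 points in both arms and the beta model has one precision, the primary OR is overstated by about 5–6% at 80/85% (1.48–1.50 against 1.417), with coverage of about 86–92%. At 85/90% it is overstated by about 11–19% (1.76–1.89 against 1.588), with coverage of about 56–83%. These figures rest on beta-distributed TIR, assumed intermediate steps, 180 per arm, and no covariates or clinic intercepts.

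A reader might infer more, and the article does not support it:

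- That all of the plan's scenarios are affected. For beta data the OR is off by only about 1–2% at 70/75% and 75/80%, with near-nominal coverage.
- That the OR is necessarily overstated at 90/95%. Both size and direction there depend on the unstated handling of values near 100%; censored-normal data even give 1.653 against 2.111.
- That the false-positive rate is generally inflated. It is not when means and SDs are equal; the 13–47% at mean TIR of 80–90% rests on an assumed SD of 12 against 10.
- That the trial is underpowered or its sample size wrong on this account. It is not.

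**What to change.** Under Models, state that the beta regression for TIR has group allocation in both the mean and the precision sub-model, with a Student's t prior on the log-precision coefficient, and report the OR from that model. Do the same for the beta model of sampling adherence, where the arms may also differ in spread.

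In the same place, fix in advance how values at or near 100% are modelled, for example with a one-inflated or ordered beta model, and define the reported effect on the overall mean. This second part is needed because precision by arm with simple clipping or shrinkage can under-cover at 90/95%. The boundary models themselves were not simulated here.

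The cost of the precision term is one parameter per beta model and a sentence or two of text. In the simulations, power moved from 99.9–100% to 96.8–96.9% at 80/85% and from 100% to 95.7–97.8% at 85/90%, a fall of about 2 to 4 points. Part of that fall is only the removal of the upward bias: a plain comparison of means had 96.3–98.1% in the same runs. No new data and no change to the 360 completers or 412 recruited are needed.

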### Measures

#### Clinical outcomes

Glycaemic control (time in range, TIR, % of time) in gestational weeks 37–38*.HbA1c in gestational weeks 37–38*.Metabolic and inflammatory biomarkers in gestational weeks 37–38.Gestational weight gain.Metformin/insulin treatment (introduction of).Adverse obstetric and neonatal outcomes (for details, see below).Maternal cardiometabolic risk profile 1 year postpartum.

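### One fixed prior scale of 2.5 for every linear model, with no stated standardisation, makes the reported effect depend on the outcome's unit

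*Protocol article*

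**What the plan says.** The Statistical analyses section sets the priors once, for all models: "All intercepts and covariates will be given Student’s t priors", and "The priors will be centred at 0 with a scale of 2.5 and 3 degrees of freedom". For reporting, "we will use medians of posterior distributions as point estimates of effects together with 95% compatibility intervals" are planned. For each outcome the plan also gives the posterior probability that the effect favours the intervention, and the range symmetric about the null that holds 95% of the posterior. It reads that range as a statement on similarity and says that the contrast bears on implementation.

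The Models section gives time in range a beta regression and then states: "We will use linear regression for all other outcomes apart from the introduction of metformin/insulin treatment". Adverse obstetric and neonatal outcomes and sampling adherence are also excepted. The linear model therefore covers the serum biomarkers at weeks 37–38 ("They will be analysed for insulin-like growth factor I", then binding proteins, copeptin, two further peptides and leptin).

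At one year the listed outcome is "Maternal cardiometabolic risk profile 1 year postpartum". The corresponding measures section says "A fasting blood sample is taken and plasma glucose, HDL-cholesterol, and triglycerides, serum insulin and insulin resistance (HOMA-IR) are assessed", and then that "based on these variables, a cardiometabolic risk score for each woman will be calculated using commonly applied standards".

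The article gives no unit, SD or distribution for any of these markers. It mentions neither transformation nor scaling.

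**The concern.** A prior scale of 2.5 has a meaning only relative to the scale of the coefficient. For a log odds ratio, as in the beta regression for time in range, or for a standardised outcome, it is wide. For a difference in pmol/L, ng/mL or grams it may be much narrower than the sampling error, and it then pulls a real difference towards zero. Changing the laboratory's unit would change the conclusion.

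Both decision quantities are exposed. Shrinkage moves the probability of benefit towards 0.5. It can also narrow the symmetric range around the null, so that an effect of the unit looks like evidence that SPARK and standard care perform alike.

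A second, smaller matter is skewness. Marker concentrations are strictly positive and often right-skewed, and a linear model on the raw scale is then less efficient than one on the log scale.

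**Working it through.** The plan has no figure of its own on this point. Only its completer number is used.

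**Inputs.** 360 completers at 1:1 give 360/2 = 180 per arm (Sample size; Randomisation and blinding). The prior is Student's t with 3 df, centre 0, scale 2.5, and is taken to cover the group term. SDs and units are assumptions, shown as ranges.

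**Formula.** SE = SD × √(2/180) = 0.1054 × SD. The posterior for the group difference is proportional to Normal(observed difference; SE) × t₃(0, 2.5), evaluated numerically. The SE is treated as known, without covariate adjustment or clinic intercepts. The SE reaches the prior scale at SD = 2.5/0.1054 ≈ 24.

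**Share of a 2.8-SE effect kept in the posterior median**

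| Outcome and unit | Assumed SD | Observed effect | Share kept | Probability of benefit (0.997 under a flat prior) |
|---|---|---|---|---|
| Triglycerides, mmol/L | 1 | 0.295 | 99.8% | 0.997 |
| HOMA-IR | 2.5 | 0.738 | 98.6% | 0.997 |
| Insulin, mU/L | 5 to 10 | 1.48 to 2.95 | 95% to 86% | 0.997 to 0.995 |
| Leptin, ng/mL | 15 to 25 | 4.43 to 7.38 | 77% to 61% | 0.992 to 0.981 |
| Insulin, pmol/L | 40 to 70 | 11.8 to 20.7 | 43% to 20% | 0.955 to 0.885 |
| Birth weight, g | 500 | 147.6 | 0.3% | 0.574 |

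The insulin rows apply only if insulin is modelled separately. The birth-weight row assumes linear regression. The article names birth weight as a continuous outcome, but lists it under neonatal outcomes, whose stated model is a count of adverse events. A weight cannot be such a count, so linear regression is the natural reading.

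**Same data, two units.** Take an insulin difference of −9 pmol/L with SE 4.7. The posterior median is −2.6, or 2.6/9 = 29% of the observed value, and the probability of benefit falls from 0.97 to 0.85. Dividing by an assumed conversion factor of 6 gives −1.5 mU/L with SE 0.78. The posterior median is then −1.35, or 90%, with a probability of about 0.96.

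**Similarity range.** Under a flat prior, the symmetric 95% range at 2.8 SE is about effect + 1.645 × SE. For insulin in pmol/L with SD 70 this is 20.66 + 1.645 × 7.38 = 32.8, and under the stated prior it is 18.0. For leptin with SD 25 it is 7.38 + 1.645 × 2.635 = 11.7, against 9.0.

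**With the prior scaled.** If the scale is 2.5 × SD, or the outcome is standardised to SD 1, 99.8% of a 2.8-SE effect is kept whatever the unit.

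**Skewness, separately.** This check used log-normal data, 180 per arm, a 15% lower geometric mean and a two-sample t-test.

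| Log-SD | Power, raw | Power, log |
|---|---|---|
| 0.4 | 96% | 97% |
| 0.5 | 82% | 86% |
| 0.6 | 65% | 73% |
| 0.7 | 50% | 59% |
| 0.8 | 37% | 48% |

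The gain is 1 to 11 points. If the effect is instead set to give 80% power on the log scale, raw power is 77% at log-SD 0.4 and 66% at 0.8. The raw-scale type I error stays at 0.048–0.053.

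**The case against.** The strongest reply is that this is a condensed article. Nowhere does it say that outcomes enter on the raw scale, and a model for a logged outcome is still linear regression. Transformation and scaling may stand in a full analysis plan that is not shown. For transformation this reply holds: a reader might infer that the plan commits to untransformed biomarkers, but that rests on silence. For the prior it holds less well. The article states the scale as an absolute number, down to the degrees of freedom, for all intercepts and covariates. Followed as printed, that rule depends on the unit. If the group term is not among the covariates, its prior is not given at all.

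A reader might also infer that insulin, HOMA-IR, triglycerides and leptin are all shrunk. The documents do not support that. The first three appear mainly as components of a composite risk score, and separate models for them are not clearly planned. The economic evaluation does refer to risk factors in the plural. Shrinkage is also negligible for HOMA-IR and for triglycerides in mmol/L. Leptin and the other serum biomarkers are the clear cases for the linear rule.

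Further points stand. The SDs and units are assumed. Covariate adjustment would reduce the SE and so the shrinkage. The difference in arithmetic means is a legitimate target, for which a linear model is valid at this sample size. The article does not base its inference on hypothesis tests, so the power figures only indicate relative precision.

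**Conclusion.** The point holds for the prior. As printed, one absolute scale of 2.5 serves every linear outcome, and its strength is set by the reporting unit. Under the assumed SDs the consequence runs from nil (triglycerides in mmol/L, HOMA-IR), through a loss of about a quarter to two fifths of the effect (leptin in ng/mL), to almost complete loss when the SD is in the hundreds. The probability of benefit and the similarity range are distorted with it.

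The skewness part is a recommendation, not an error. It gains about 1–11 points of power at log-SD 0.4–0.8 for a 15% lower geometric mean, and type I error is not at risk.

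A reader might infer that the primary results are undermined. The calculation does not support that. Time in range is modelled on the log-odds scale, where 2.5 is wide. HbA1c does fall under the linear rule, but for any SD up to 5 in its reporting unit at least 95% of a 2.8-SE effect is kept. The outcomes materially affected are secondary, so the severity is minor to moderate.

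**What to change.** Add to Statistical analyses that continuous outcomes and continuous covariates are standardised before fitting, or that the prior scale is 2.5 times the outcome SD (with the matching rescaling for continuous covariates), and that estimates, intervals and similarity ranges are reported in original units. If the software already rescales the priors, say so.

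Add to Models that strictly positive, right-skewed concentrations are analysed on the natural-log scale, with the log baseline value where available, and reported as ratios of geometric means. Examples are leptin and copeptin, and insulin, HOMA-IR and triglycerides if these are modelled separately. Say also which model applies to birth weight and length.

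The cost is two or three sentences, fixed before outcome data are examined, with no change to data collection or sample size. The one real downside is that logging changes the estimand to a ratio, so differences in raw units need a separate back-calculation. Scaling the prior has no such cost.

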#### Adverse obstetric and neonatal outcomes

Information about obstetric and neonatal outcomes are collected as continuous variables or incidence from electronic medical records including its registry (Obstetrix, ORACLE Cerner, Sweden). They include, for instance, the incidence of pre-eclampsia, pregnancy-induced hypertension, metformin/insulin treatment, gestational week at birth, induction of labour, caesarean sections, vacuum-assisted delivery, epidural anaesthesia, glucose-insulin treatment during delivery, infant Apgar score at 1, 5 and 10 min, incidence of large-for-gestational-age infants, macrosomia (>4500 grams), infant shoulder dystocia, infant hypoglycaemia and length of hospital stay. We will also evaluate infant birth weight and length as continuous variables as outcomes.

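### A negative binomial count is the only model for an adverse-outcome family that mixes morbidity, treatments, procedures and non-event measures

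*Protocol article*

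**What the plan says.** Three places in the protocol article bear on this.

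- **Statistical analyses, Models.** The family's model is given as "adverse outcomes will be modelled using negative binomial regression (counting the number of incidences adverse outcomes". Adverse obstetric and neonatal outcomes are named, as a block, among the exceptions to linear regression. Drug treatment is a separate exception: "The introduction of metformin/insulin treatment will be modelled using ordinal regression (no treatment<metformin<insulin".
- **Measures, Clinical outcomes.** "Metformin/insulin treatment (introduction of" appears as its own entry, apart from the entry for adverse obstetric and neonatal outcomes.
- **Measures, Adverse obstetric and neonatal outcomes.** The data are "collected as continuous variables or incidence from electronic medical records". The list is open and begins "They include, for instance, the incidence of pre-eclampsia, pregnancy-induced hypertension, metformin/insulin treatment, gestational week at birth, induction of labour, caesarean sections". It continues "vacuum-assisted delivery, epidural anaesthesia, glucose-insulin treatment during delivery, infant Apgar score at 1, 5 and 10 min" and ends with "incidence of large-for-gestational-age infants, macrosomia (>4500 grams), infant shoulder dystocia, infant hypoglycaemia and length of hospital stay". A further sentence adds birth weight and birth length as continuous outcomes.

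The Statistical analyses section also says that each outcome will be reported with the posterior probability that the effect favours the intervention arm.

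**The concern.** A per-woman sum of events is the natural reading of the model sentence, and the list under the matching heading is not a list of comparable events. An epidural would add one, exactly as shoulder dystocia does. A very large infant could add two. Items driven by care decisions are common, so they could carry most of the total, and a real reduction in morbidity would then show as a small change in the count.

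The treatment items raise a second problem. Each outcome is reported in the direction of favouring one arm, so a treatment item inside the count makes the arm that treats more look worse. The arms differ in how clinicians are alerted: SPARK flags out-of-range glucose values automatically, while control women have a weekly review. Care is not blinded. A difference in treatment rates is therefore plausible, in either direction.

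Finally, gestational week, Apgar score and length of stay cannot be counted as incidences, yet the family is excluded from linear regression. At stake is the answer to aim (d), on adverse obstetric and neonatal outcomes.

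**Working it through.** **Step 1: the list against the model.** The plan gives no rate, effect size or power for this count, so there is no stated figure to reproduce. The listed items sort as follows.

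| Type | Items listed | Fit with a count of adverse events |
|---|---|---|
| Morbidity | pre-eclampsia, pregnancy-induced hypertension, large-for-gestational-age, macrosomia, shoulder dystocia, infant hypoglycaemia | Fits, but large-for-gestational-age and macrosomia overlap |
| Drug treatment | metformin/insulin | Conflicts with its separate listing and ordinal model |
| Management | induction, caesarean, vacuum delivery, epidural, intrapartum glucose-insulin | Countable, but care processes |
| Non-event | gestational week at birth, Apgar, length of stay, birth weight and length | Not incidences; removed from linear regression with the family |

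**Step 2: size of the dilution.** All risks below are assumptions; none comes from the document. Pre-eclampsia 5%, pregnancy-induced hypertension 5%, large-for-gestational-age 20%, macrosomia 5%, dystocia 2%, infant hypoglycaemia 15%; metformin/insulin 30%; induction 35%, caesarean 25%, vacuum 6%, epidural 40%, intrapartum glucose-insulin 10%.

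The expected count is the sum of the risks:

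- morbidity: 0.05 + 0.05 + 0.20 + 0.05 + 0.02 + 0.15 = 0.52 (0.47 with macrosomia left out)
- management: 0.35 + 0.25 + 0.06 + 0.40 + 0.10 = 1.16
- total without metformin/insulin: 0.52 + 1.16 = 1.68, of which 1.16/1.68 = 69% is management
- total with metformin/insulin: 1.68 + 0.30 = 1.98; morbidity without macrosomia is 0.47/1.98 = 24% of it

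A 25% fall in morbidity removes 0.25 × 0.52 = 0.13 events per woman. The count ratio is the SPARK expectation divided by the control expectation.

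| Case | Control | SPARK | Ratio |
|---|---|---|---|
| Morbidity only | 0.52 | 0.39 | 0.75 |
| Without metformin/insulin, care unchanged | 1.68 | 1.68 − 0.13 = 1.55 | 0.92 |
| Without metformin/insulin, intrapartum treatment +5 points | 1.68 | 1.55 + 0.05 = 1.60 | 0.95 |
| With metformin/insulin, care unchanged | 1.98 | 1.98 − 0.13 = 1.85 | 0.93 |
| With metformin/insulin +10 points, intrapartum +5 points | 1.98 | 1.85 + 0.15 = 2.00 | 1.01 |
| With metformin/insulin −10 points | 1.98 | 1.85 − 0.10 = 1.75 | 0.88 |

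**Step 3: other assumptions.** Take 0.4 to 0.8 morbidity events and 0.8 to 1.2 management items per woman (equal in both arms), and a true 10% fall in morbidity. Without drug treatment, the ratio of 0.90 becomes 0.95 (1.52/1.60) to 0.975 (1.56/1.60). With drug treatment included and rising from 20% to 25%, 20% to 30% or 25% to 40%, it is 0.98 (1.77/1.80) to 1.08 (1.56/1.45). With no true morbidity effect, the same rises give 1.02 (2.25/2.20) to 1.10 (1.60/1.45).

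**Step 4: the other reading of the model sentence.** If one negative binomial model per outcome is meant, each item is 0 or 1. Its variance/mean ratio is p(1 − p)/p = 1 − p, always below 1, and a negative binomial does not allow a ratio below 1. That reading does not fit either.

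**The case against.** The strongest reply is that the document never says metformin/insulin is in the count. Clinical outcomes lists it separately and Models gives it an ordinal model. That stands. A reader might infer that earlier treatment prompted by SPARK would score as harm, but the documents do not support this. The Measures list conflicts with the other two places rather than settling the matter, and an incidence count registers whether treatment occurred, not when. More treatment under SPARK is also an inference. The app includes a diet and activity programme, and the Introduction says lifestyle change suffices for 70%–85% of women, so treatment could fall; the last row of the table in Step 2 shows that case.

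A reader might also infer that continuous variables are to be summed. The Models section counts incidences, so this is not what it says. The narrower defect is that the block exclusion leaves the non-event measures without a fitting model. For birth weight and length, linear regression may well be intended, but the exclusion leaves that unstated.

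A third reply is that the list is illustrative and the components may be fixed in an SAP that is not shown. Missing detail alone would not be a point. Here, however, both the model and its input list are stated, and they do not fit each other. Likewise, the article's silence on whether single events will also be reported separately is not a fault.

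Under-dispersion of the summed count is a weak argument. With independent items at the assumed risks, the variance/mean ratio is 1.461/1.98 = 0.74, but an average pairwise correlation of about 0.04 would remove the shortfall. The conclusion does not rest on it.

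**Conclusion.** The point holds as a moderate one. Three things are in the text: metformin/insulin is placed both inside and outside the family; procedures and overlapping events are listed under a heading whose only model is a count; and non-event measures are excluded from linear regression with nothing suitable in its place.

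The size depends on assumed risks. Dilution persists even when metformin/insulin is left out: a morbidity ratio of 0.75 becomes about 0.92 to 0.95. Masking to about 1.01 requires that metformin/insulin is counted and rises by 10 points, with intrapartum treatment up by 5. Even that is a null result, so a general claim that SPARK would be scored as harmful goes too far. The primary outcomes, time in range and HbA1c, are unaffected.

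**What to change.** - Reconcile Clinical outcomes, Adverse obstetric and neonatal outcomes, and Models, so that each variable belongs to one outcome with one model.
- Confine the count to named binary maternal and infant morbidity events, taking one of each overlapping pair (large-for-gestational-age or macrosomia). State whether pre-eclampsia and pregnancy-induced hypertension can both score for one woman.
- Keep metformin/insulin only in its ordinal model. Report induction, caesarean, vacuum delivery, epidural and intrapartum glucose-insulin separately.
- Model individual binary outcomes by multilevel logistic regression, using the clinic intercepts already planned.
- Name models suited to the type of gestational week at birth, Apgar score, length of stay, and birth weight and length.

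The cost is some wording and a few more models on data already to be extracted. There will be more estimates to report, several with wide intervals. Settling this before outcome data are seen also prevents a later choice of components from an open list.
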